#### Criteria for discontinuing or modifying allocated interventions {11b}

The intervention will stop in the following circumstances:

Patients who developed planned or unplanned catheter removal;Discharge, death, deterioration of the condition;Patients withdraw proactively;Wrong intervention.

#### Strategies to improve adherence to interventions {11c}

Before the start of the study, each centre will designate several nurses to perform the intervention. These nurses are competent in clinical practice. To exclude the influence of operational error on the study results, the leading unit conducted training to ensure that these nurses are familiar with the study. In addition, the leading unit has shot videos to standardize each operator’s practice. During the study, the leading unit will send coordinators to other centres to check protocol implementation, the most important of which is whether the intervention is regulated.

#### Relevant concomitant care permitted or prohibited during the trial {11d}

This is a randomized controlled study, and contamination between the two groups should be avoided. Therefore, pulsative flushing is prohibited for the test group.

#### Provisions for post-trial care {30}

After the trial, participants in both groups will resume routine care. There are no expected injuries or compensation for participation in the trial.

#### Outcomes {12}

The primary outcome of this study is occlusion rate in 7 days. Catheter occlusion will be assessed by scoping CINAS. The CINAS [25] is an instrument used to assess catheter function. It has two dimensions: injection ability (IN) and aspiration ability (AS). Each dimension includes four classifications: (1) easy, (2) difficult, (3) impossible, and (4) unknown. The CINAS comprises 16 possible ways to combine four distinct codes (Table 1). Each combination represents the ability to inject at least 1 ml of fluid and to aspirate at least 3 ml of blood and is graded on a scale of 1 to 3 (1 being easy, 2 being difficult, and 3 being impossible). When the injection and/or aspiration ability is unknown, a fourth classification option is provided (X).

**Table 1 Tab1:**
[figure not shown]
The Catheter Injection and Aspiration (CINAS) [25]

The secondary outcomes of this study include the 3-day catheter occlusion rate, which is also assessed by scoping CINAS, nurse satisfaction, and cost-effectiveness. Nurse satisfaction is defined as nurses’ attitudes towards these two different methods of flushing catheters. This outcome will be assessed by scoping a 5-point Likert scale (1 = Very dissatisfied, 2 = Dissatisfied, 3 = Unsure, 4 = Satisfied, 5 = Very satisfied). Cost-effectiveness will be assessed by calculating related medical expenses and nursing time and analysing the effect of the two methods.

The safety outcomes of this study are adverse event rates and intravenous therapy-related complications. The adverse events include unplanned removal, unplanned thrombolysis, and elastic pump failure. All these adverse events are defined as follows:

(I)Unplanned removal: intubation accidental dislodgement or removal of the catheter by the patient without the consent of the health care provider. This removal may also be the result of improper handling by the health care provider.(II)Unplanned thrombolysis: a thrombotic occlusion of the patient’s CVC and the CVC needs to be recanalized with a thrombolytic drug such as a fibrinogen activator.(III)Elastic pump failure: elastic pump breakage.

Intravenous therapy-related complications include CRBSI, catheter-related thrombosis (CRT), catheter misplacement, extravasation, and phlebitis. The definitions of these metrics are shown below:

(I)CRBSI: bacteraemia or fungemia in a patient with an intravascular catheter or within 48 h of removal of an intravascular catheter with manifestations of infection such as fever (38 °C), chills, or hypotension, with no clear source of infection other than the vascular catheter. Laboratory microbiology reveals positive peripheral venous blood cultures for bacteria or fungi or pathogenic bacteria of the same species with the same drug-sensitive results from the catheter segment and peripheral blood cultures.(II)CRT: a mural thrombus extending from the catheter into the lumen of a vessel, leading to partial or total catheter occlusion with clinical symptoms that was established by Doppler colour flow imaging.(III)Catheter misplacement: the position of the catheter tip changes.(IV)Extravasation: fluid or drug extravasation.(V)Phlebitis: this includes chemical phlebitis, mechanical phlebitis, and infectious phlebitis. Clinical signs and symptoms include pain, pressure, erythema, and erythema. Grades will be assessed according to the phlebitis scale in the INS guidelines [22].

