Keep vein open (KVO) refers to the practice of keeping a vein open with a small amount of intravenous solution [16]. Previous studies have focused mainly on comparing the effects of intermittent flushing and continuous infusion on peripheral intravenous catheters and neonates [17, 18]. However, none of these studies have offered a comparison in the adult population. In this study, we will ameliorate KVO infusion and use it in the adult population. We will use an elastic pump to run continuous infusion rather than gravity infusion. This kind of elastic pump contains 50 ml of 0.9% sodium chloride solution, and KVO infusion can be applied at a rate of 2 ml/h. KVO infusion was used between doses of intermittent medication in previous studies. In this study, participants will receive a whole-day KVO infusion, regardless of whether the participants are on intermittent medication.

Studies [19–21] have shown that the use of an elastic pump achieves the same results as heparin locking in general surgery patients with discontinuous infusions using single-lumen central venous catheters and in the maintenance of peripheral venous catheters, ensuring 100% catheter patency. The elastic pump infusion technique is designed to maintain the infusion pressure at 55 kPa, which is much higher than the human central venous pressure (0.5 ~ 1.2 kPa), by adopting the clinical micropump and infusion pump precision infusion principal technique and the built-in flow limiter, which can achieve continuous dynamic infusion and maintain catheter patency.

It is worthwhile to further investigate what kind of flushing technique can better ensure the patency of anterior-open multilumen central venous catheters (CVCs), which are widely used in continuous infusions, to ensure the safety of patient treatment and ease of movement. We completed a pretest with a sample of 20 patients to test the effectiveness of the KVO flushing technique for maintaining the patency of dual-lumen CVCs. The experimental results showed that no catheter occlusion occurred in the test group, while two cases of catheter occlusion occurred in the control group. Therefore, our team plans to expand the sample size and design a multicentre clinical control trial to test the effectiveness of this technique.

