#### Intervention description {11a}

The placement and maintenance of CVCs are carried out by trained and qualified professionals. Disinfectants that meet Chinese regulations [23] are selected for puncture and maintenance, creating a maximum sterile barrier and using a uniform catheter placement process. We previously standardized the type of CVC (FORNIA, CVC-2 7F 20) to be applied in this study to reduce interference. In addition to the flushing technique, other care measures for the catheter will be carried out according to the same standard, including using the same infusion connector (BD Luer-Lok™ 394605), changing the dressings once a week**,** and changing the infusion once a day; in special cases, the frequency of replacement will increase.

Depending on the grouping, patients in the test group will undergo KVO infusion using an elastic pump containing 50 ml of 0.9% sodium chloride solution, which maintains a constant pressure (55 kPa) and a steady infusion rate (2 ml/h). Before daily infusion, the study nurses will mechanically wipe and disinfect the infusion connector, connect the stopcocks according to the infusion demand, connect the elastic pump to the female opposite port of the endmost stopcocks, connect the medication pathways to the female side ports, adjust the stopcocks handle for infusion and flushing, and fix the elastic pump appropriately to observe the liquid in the elastic pump and pumping situation at regular intervals. At the end of the infusion, the stopcock handle will be adjusted to close the medication pathway, and the pumping of the elastic pump will be continued. The study nurses will change the pumps once a day. The elastic pump pumping valve will be closed, the elastic pumps will be separated from the stopcocks or catheters, and the stopcocks will be mechanically disinfected. Two new elastic pumps will then be connected, the handle will be adjusted to continue pumping, and the elastic pumps will be properly fixed to ensure that it does not interfere with patient activities.

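### Elastic pump failure is defined only as breakage, so a pump that stops, slows or empties early without breaking is left out of the reported failure rate

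*Protocol article*

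**What the plan says.** Outcomes {12} lists three adverse events within the safety outcomes: unplanned removal, unplanned thrombolysis and elastic pump failure. Each gets a definition. The third reads in full: "Elastic pump failure: elastic pump breakage".

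Other sections describe what the pump is for:

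- Background and rationale {6a}: "This kind of elastic pump contains 50 ml of 0.9% sodium chloride solution, and KVO infusion can be applied at a rate of 2 ml/h". It adds that "participants will receive a whole-day KVO infusion, regardless of whether the participants are on intermittent medication".
- Intervention description {11a}: the test group has "KVO infusion using an elastic pump containing 50 ml of 0.9% sodium chloride solution", at constant pressure and a steady rate. "The study nurses will change the pumps once a day". Nurses are also to "observe the liquid in the elastic pump and pumping situation at regular intervals".
- Relevant concomitant care {11d}: pulsatile flushing is not allowed in the test group.
- Adverse events reporting and harms {22}: adverse events and unforeseen consequences of every kind are to be assessed and documented, and study nurses look for complications each day.

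**The concern.** The pump is the experimental intervention, and what it has to do is deliver a steady flow all day. The failure outcome does not measure loss of that function. It measures one physical cause of loss. An intact pump that stalls, runs clearly slow or is empty before it is replaced has failed at its task but does not meet the definition.

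Two things are at stake. The first is the safety report: a reader who sees a low pump-failure rate will take it as evidence that the device delivers reliably, when it shows only that the device seldom breaks. The second is interpretation. If the test arm does less well than hoped, the failure outcome will not help to tell a technique that does not work from a pump that did not deliver, and the article names no substitute flush for a lumen whose pump has stopped.

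**Working it through.** **Inputs, all from the protocol article**

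- Pump volume: 50 ml (Background {6a}; Trial design {8}; Intervention description {11a}).
- Flow rate: 2 ml/h, described as steady, with no tolerance given (same sections).
- Pump change: once a day, taken here as 24 h (Intervention description {11a}).
- Failure definition: breakage (Outcomes {12}).

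The article states no run time, so there is no figure of its own to reproduce. The sample size of 125 per group does not depend on this point.

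**Step 1. Run time.** Volume / rate = 50 / 2 = 25 h.

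**Step 2. Reserve.** 25 − 24 = 1 h. Volume left at 24 h = 50 − 2 × 24 = 2 ml. At the stated rate and a 24 h change the pump does not run dry.

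**Step 3. What uses up the reserve.** The rate that empties the pump at exactly 24 h is 50 / 24 = 2.083 ml/h, and 2.083 / 2 − 1 = 4.2% above nominal. At the nominal rate, a change more than 1 h late does the same.

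**Step 4. Sensitivity.** The deviations below are assumptions made to show a range. Run time = 50 / [2 × (1 + deviation)].

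| Assumed flow deviation | Pump empties at | Time without pump flow before a 24 h change |
|---|---|---|
| −10% | 27.8 h | none |
| 0 | 25.0 h | none |
| +5% | 23.8 h | 0.2 h |
| +10% | 22.7 h | 1.3 h |
| +15% | 21.7 h | 2.3 h |

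At nominal flow, a change at an assumed 26 h leaves 26 − 25 = 1 h without pump flow, and one at 28 h leaves 3 h. These are hours without pump flow, not hours without any flow in the catheter.

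**Step 5. Which events the definition captures**

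| Event | Pump failure under Outcomes {12}? | Where else it may appear |
|---|---|---|
| Pump breaks | Yes | Adverse event record |
| Pump empties before its change, intact | No | Nurse observation {11a}; general record {22} |
| Flow stops or is clearly slow, pump intact | No | Nurse observation {11a}; general record {22} |
| Catheter occludes as a result | Not in itself | Primary outcome {20a} |

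Steps 1 to 4 show that lapses in the second row are plausible on the article's own figures. Step 5 shows that such lapses stay outside the named outcome.

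**The case against.** The best case for the plan is that the figures agree and the events are not lost. Most of that stands, and it rules out several stronger readings.

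- *A reader might infer that pump capacity contradicts the change schedule.* It does not: 25 h covers a 24 h change. Running dry needs fast flow or a late change, and the article states neither. The absence of a maximum interval, or of form fields for connection time and residual volume, is operating detail that a condensed article can leave to the full protocol.
- *A reader might infer that such lapses are never counted.* That is too strong. Nurses watch the liquid and the pumping, section {22} calls for a record of every unexpected event, coordinators check the intervention on site {11c}, and any resulting occlusion enters the primary outcome. What is true is narrower: a lapse without breakage is not counted as pump failure.
- *A reader might infer that an empty pump leaves the lumens without flow.* Eligibility {10} requires at least 16 h of continuous infusion a day, and medication runs through the same stopcocks. An empty pump matters mainly for a lumen with no medication running.
- *A reader might infer a risk of false superiority.* A delivery lapse can be expected to raise test-arm occlusion if it does anything. The trial also compares the technique as delivered, so poor pump performance belongs in the primary comparison.
- *A stopcock left closed* is an operator deviation, not a failure of the device, and does not belong in this outcome.

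None of this cures the definition. An event noted at the bedside or entered in a general record does not reach the pump-failure rate while that rate counts only breakage.

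**Conclusion.** The point holds as a matter of definition. The safety outcome called elastic pump failure captures breakage and omits other loss of delivery by the pump, so the reported rate can understate device malfunction. It is a descriptive rate in one arm, because only the test group uses the pumps.

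The size of the understatement cannot be computed: the article gives neither a flow tolerance nor any frequency of early emptying or stalling. What can be said is that the reserve is 1 h, or 2 ml, and that flow above 2.083 ml/h (+4.2%) or a change more than 1 h late exhausts it. This rests on the stated volume and rate and on reading once a day as 24 h.

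The sample size and the primary estimate as planned are unaffected. Any effect on the primary outcome would go against the test arm, on the assumption that loss of pump flow does not lower occlusion. The consequences are therefore a device-failure rate that can look too favourable and a weak or null result that would be harder to interpret.

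**What to change.** In Outcomes {12}, define elastic pump failure as any loss of intended delivery attributable to the pump: breakage, emptying before the scheduled change, or stopped or clearly slow flow. Classify the events noted during pump observation {11a} and those recorded under Adverse events reporting {22} by that definition. Report breakage and non-breakage failures separately, so that the breakage count remains visible.

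The cost is a changed definition and a pass through the existing records. The downside is a higher reported pump-failure rate. Trial status gives 31 July 2023 as the end of data collection, so for this trial the classification can use only what was written down. The report should say so and state the original definition beside the wider one. No rate, volume or change interval is proposed here; those remain for the sponsor.

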**Method:**

This is a randomized controlled trial of 14 hospitals in China. A total of 250 patients will be recruited in this study, and they will be randomized at a 1:1 ratio. After study inclusion, patients who will undergo CVC insertion will receive intermittent flushing with prefilled saline syringes (control group) or KVO infusion with elastic pumps (test group). All the catheters will be checked for patency by scoping Catheter Injection and Aspiration (CINAS) Classification on Days 3 and 7. The primary outcome is the rate of catheter occlusion in 7 days. Patients will be followed up until 9 days after CVC insertion, catheter occlusion, or catheter removal. The secondary outcomes are the rate of catheter occlusion in 3 days, nurse satisfaction, cost-effectiveness, adverse event rate, catheter-related bloodstream infection rate, catheter-related thrombosis rate, extravasation rate, phlebitis rate, and catheter migration.

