In the control group, prefilled saline syringes containing 10 ml of 0.9% sodium chloride injection will be used to flush and lock the catheter via pulsatile flushing and the positive pressure locking technique. Before each infusion, the study nurses will mechanically wipe and sterilize the infusion connector. Catheter function will be assessed by flushing the catheters and aspirating for blood return. After seeing the blood return, the catheter will be flushed using short-interval pulsatile flushing (1 ml each time), for a total of 10 ml [22]. At the end of the infusion, prefilled saline syringes will be used to flush each lumen (even if only one lumen is used) via pulsatile flushing and the positive pressure technique [24].

The study will continue for 7 days unless there is catheter occlusion or catheter removal. During the 7 days, the study nurses will identify catheter occlusion by scoping the CINAS, observing the infusion status, and identifying the occlusion alarm. Once catheter occlusion occurs, the patients reach the end of the study, and the management of the blocked catheter will be referred to the physician and nurse. The end of the trial also includes a 2-day observation period, which will monitor the occurrence of catheter-related bloodstream infection (CRBSI), primarily through temperature monitoring.

Throughout the trial, the study team will fully respect the patient’s wishes, and the patients will have the right to withdraw from the trial. In addition, if a patient has no observed occlusion during the trial period and removes the CVC for other reasons, then the patient will be considered to have dropped out.

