#### Methods in analysis to handle protocol non-adherence and any statistical methods to handle missing data {20c}

For possible missing data during the study, the analysis will be carried forward for missing primary outcomes, and the specific carryover method is described in “Statistical methods for primary and secondary outcomes {20a}” section. Catheter occlusion is defined as a partial or complete occlusion of an intravascular catheter, resulting in blocked or restricted infusion of fluid or medication. For subjects who failed to complete the primary outcome evaluation, the method of worst-case imputation will be used to handle missing values. That is, if subjects withdraw early or for any other reason and the primary outcome is missing, the decision of whether or not catheter occlusion occurred will be treated as occlusion.

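### Catheter-related thrombosis is counted only when it occludes the catheter, so its rate is not safety evidence independent of the primary outcome

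*Protocol article*

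**What the plan says.** **Role of CRT.** The safety outcomes under Outcomes {12} state: "Intravenous therapy-related complications include CRBSI, catheter-related thrombosis (CRT), catheter misplacement, extravasation, and phlebitis". The Abstract (Method) also places it among the secondary outcomes: "catheter-related bloodstream infection rate, catheter-related thrombosis rate, extravasation rate, phlebitis rate, and catheter migration".

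**Definition of CRT.** The only definition in the article, in the list of complications under Outcomes {12}, describes a thrombus on the vessel wall that starts at the catheter and is one "leading to partial or total catheter occlusion with clinical symptoms"; Doppler imaging must confirm it. Four elements are needed together: mural thrombus, catheter occlusion caused by it, symptoms, and Doppler confirmation.

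**Primary event.** Outcomes {12} says "The primary outcome of this study is occlusion rate in 7 days". The formula in section {20a} adds complete and partial occlusions in the numerator, and section {20c} says "Catheter occlusion is defined as a partial or complete occlusion of an intravascular catheter".

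**Follow-up.** Under Intervention description {11a}, "Once catheter occlusion occurs, the patients reach the end of the study". The Abstract likewise ends follow-up at day 9, occlusion or removal, whichever applies. Table 2 schedules complication records through days 8 to 9, but patency assessment only through day 7.

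**General recording.** Section {22} names occlusion and thrombosis as separate expected complications and provides for all adverse events to be recorded.

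**The concern.** A safety outcome should be able to move independently of the efficacy outcome. Here the occlusion that defines the primary event is also an entry condition for CRT. The test technique is meant to keep the lumen open. If it does so without preventing thrombus on the vessel side, some test-arm patients could have a symptomatic, imaged thrombus and a catheter that still flows. Under the printed definition they are not CRT cases.

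Two things are at stake. First, the CRT rate understates symptomatic thrombosis in both arms. Second, a lower CRT rate in the test arm could be presented as a thrombosis benefit when it partly or wholly restates the occlusion result.

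**Working it through.** **Step 1. Set the definitions side by side.**

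| Element | CRT, Outcomes {12} | Primary event, {20a} and {20c} |
|---|---|---|
| Catheter occlusion, partial or full | required | required |
| Mural thrombus | required, as the cause | not required |
| Symptoms | required | not required |
| Doppler confirmation | required | not required |

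Every CRT is thus an occlusion with further conditions attached. No section counts a thrombus with a patent catheter as CRT. The nesting is within occlusion generally, not strictly within the 7-day primary event: complications are recorded to day 9, so an occlusive CRT on day 8 or 9 would lie outside the primary outcome.

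**Step 2. Reproduce the planning figures used below.** Sample size {14} assumes occlusion of 25% (control) and 10% (test), one-sided alpha 0.025, power 0.8 and 20% dropout. With pooled variance and mean proportion 0.175:

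n = [1.960 × √(2 × 0.175 × 0.825) + 0.842 × √(0.25 × 0.75 + 0.10 × 0.90)]² / 0.15² = 99.5, rounded up to 100 per arm.

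100 / (1 − 0.20) = 125 per arm, which is the stated figure. This point does not dispute it.

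**Step 3. Write down what is recorded.** Let t be the true rate of symptomatic mural thrombosis, assumed equal in both arms. Let q_T and q_C be the chances that such a thrombus occludes the catheter in the test and control arms. The article gives none of these.

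Recorded CRT rate = t × q, so the recorded test/control ratio = (t × q_T) / (t × q_C) = q_T / q_C. The true rate cancels; only the ratio of the two chances matters.

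**Step 4. Put in illustrative values.** Expected counts per 125 patients are 125 × t × q.

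| Assumed t | True cases per arm | q_C, q_T | Recorded control | Recorded test | Ratio |
|---|---|---|---|---|---|
| 2% | 2.50 | 0.25, 0.10 | 0.62 | 0.25 | 0.40 |
| 5% | 6.25 | 0.25, 0.10 | 1.56 | 0.62 | 0.40 |
| 10% | 12.50 | 0.25, 0.10 | 3.12 | 1.25 | 0.40 |
| 20% | 25.00 | 0.25, 0.10 | 6.25 | 2.50 | 0.40 |
| 5% | 6.25 | 0.75, 0.30 | 4.69 | 1.88 | 0.40 |
| 5% | 6.25 | 0.50, 0.50 | 3.12 | 3.12 | 1.00 |
| 5% | 6.25 | 1.00, 1.00 | 6.25 | 6.25 | 1.00 |

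The first four rows carry the planned occlusion rates over to patients with a thrombus. The fifth makes occlusion three times as likely given a thrombus and keeps the ratio. In the sixth, half the cases go uncounted but the arms are treated alike. In the last, every thrombus occludes and nothing is lost.

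**The case against.** **A symptomatic thrombus that impairs function may be a deliberate endpoint.** That is a legitimate choice, and the article is not inconsistent in making it. It does not make the resulting rate independent of the primary outcome.

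**The direction of bias is not established.** A reader might infer that recorded CRT must favour the arm with fewer occlusions. The documents do not support that. The definition is causal: the thrombus must lead to the occlusion. The Background lists other causes of occlusion, such as catheter folding, drug properties and improper flushing. If the test technique prevented only those, q would be equal across arms and there would be no between-arm bias. This objection stands in full.

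**The 0.40 is not an estimate.** It is 10/25 restated, and applying overall occlusion rates to patients with a thrombus fits poorly with a causal definition. It shows how the mechanism works and nothing more. Nor are 10% and 25% ceilings on CRT; they are sample-size assumptions.

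**Harm would not necessarily go unseen.** A reader might infer that thrombosis with a patent catheter is lost to the trial. Section {22} and Table 2 provide for general recording of adverse events and complications, so such a case may well be on file. It would still not enter the CRT rate.

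**The numbers are small.** At an assumed t of 8%, the planned rates give 125 × 0.08 × 0.25 = 2.5 against 125 × 0.08 × 0.10 = 1.0 recorded cases. Even 3 against 1 has a two-sided Fisher p of about 0.62. CRT plays no part in the superiority conclusion. This limits the weight of the point, though a rate can be misread without being significant.

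**Broadening the count brings its own imbalance.** Follow-up ends at occlusion, so the arm with more occlusions is observed for less time. This is correct, and the fix has to allow for it.

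**Conclusion.** The definitional point holds on the text alone: CRT requires catheter occlusion, symptomatic thrombosis around a patent catheter is not counted in either arm, and the CRT rate is not safety evidence independent of the primary outcome.

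Bias between arms is conditional. Recorded CRT would favour the test arm at equal true thrombosis only if the continuous infusion lowers the chance that a thrombosed catheter occludes. The illustrated ratio runs from 0.40, if that chance followed the planned occlusion rates, to 1.00, if it were the same in both arms. The article gives no CRT rate and no conditional occlusion rate, so the size cannot be fixed further.

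This is an inexpensive improvement to a safety comparison. It does not touch the primary analysis.

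**What to change.** 1. For the safety comparison, count every symptomatic, Doppler-confirmed catheter-related thrombus, whether or not the catheter is occluded.
2. Tabulate these by arm, with and without occlusion. The with-occlusion row preserves the printed definition.
3. Show observed catheter-days per arm beside the counts, because follow-up stops at occlusion and time at risk may differ between arms.
4. Trial status gives July 31, 2023 for completed data collection, so a new case report form item may no longer be possible. Non-occlusive thrombi would then have to be sought in the complication and adverse event records. If they cannot be recovered, the report should state that CRT required occlusion and is not independent of the primary outcome.

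**Cost.** One definition line, one extra split in a safety table, a catheter-day total per arm and a search of existing records. No additional imaging or patients are asked for. The article does not say what prompts a Doppler examination, so the count of non-occlusive thrombi will reflect local practice, and the report should say so. The broader rate is slightly less comparable with rates on the narrower definition; tabulating both offsets this.
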